### Recruitment

The recruitment phase opened in March 2019 and closed on 30th November 2020 to allow sites time to recruit a sufficient sample of suitable families to the research. Unfortunately, the funding timeline means that we cannot further extend the enrolment period in order to account for the 4-month suspension caused by the COVID-19 lockdown restrictions, and as such, recruitment rates will be affected. As indicated above, the early phase of the current study involved a prior installation and implementation period in order to allow sites to train and gain experience in delivering FT [9]. Families (parents and children 5–18 years) will be recruited by clinicians in each site from their existing waiting lists. Recruitment brochures and posters will be used to inform families and clinicians about FT and the PRIMERA research. In addition, each site has nominated a lead contact person who will take responsibility for promoting FT and the PRIMERA research within their area in order to encourage referrals.

Clinicians will meet with families to assess their suitability for FT and the research process using the eligibility criteria outlined above. Once the clinician has secured agreement from the parent that they are interested in participating, they will ask for their written consent (on the family recruitment leaflet) for their contact details to be passed in confidence to the research team. Parents will then be contacted by the research team via telephone to arrange for one of the research team to talk to them in more detail about the study and to arrange to visit them to tell them more about the research and obtain their written informed consent in person. Two children per family—aged 8–18 years—are eligible to participate and their written assent will be obtained once their parent has provided prior consent for their child’s participation. Written informed consent/assent will be obtained at each data collection time point, and also if a parent/child is asked to participate in a qualitative interview. Families will be incentivised to participate with a shopping voucher worth €20 at each data collection visit. Families will be informed within 2 weeks about their allocated group.

Given the traditional segregation of adult and child mental health services in Ireland, it is expected that some clinicians and managers will not see a family-focused service as fitting their role and remit. Therefore, throughout the study, we will spend considerable time on awareness raising activities and liaison with mental health professionals (via meetings, stakeholder events) around the need to provide family-focused mental health services to support this neglected population. We will monitor the referral rates across all sites and will problem-solve with clinicians on strategies to increase recruitment if and when such issues emerge. Collectively, the research team have considerable experience of working with vulnerable and difficult-to-engage populations, and their expertise, in conjunction with the advice and support of collaborating sites, will be important in managing the recruitment process.

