**Methods:**

The study comprises a multi-centre, randomised controlled trial (RCT), with nested economic and process evaluations, to assess the clinical and cost-effectiveness and implementation mechanisms of Family Talk compared to usual services. The study is being conducted in 15 adult and child mental health settings in Ireland. Families with a parent with mental illness, and children aged 5–18 years (*n* = 144 families) will be randomised to either the 7-session Family Talk programme (*n* = 96) or to standard care (*n* = 48) using a 2:1 allocation ratio. The primary outcomes are child psychosocial functioning and family functioning. Secondary outcomes are as follows: understanding and experience of parental mental illness, parental mental health, child and parental resilience, partner wellbeing and service utilisation. Blind assessments will take place at pre-intervention and at 6- and 12-month follow-up.

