Family functioning has not been typically assessed in previous evaluations of FT despite the fact that enhanced family communication and cohesion are key intervention goals. One previous study has assessed family functioning using intensive clinician interviewing of families [25], although it should be noted that two ongoing evaluations of FT have included it as an outcome, albeit using measures that take considerably longer to administer than the SCORE-15 [28, 29]. The SCORE-15 has been used as a brief measure of family functioning in evaluations of family therapy with populations that share a clinical profile similar to the sample in the current study [53]. An effect size of 0.5 was reported. Similar to above, we conducted a G*Power *t*-test calculation for the difference between two independent means (two groups) for the outcome of family functioning. Assuming *α* = .05, 80% power, two tailed testing, 15% attrition, and 2:1 allocation, the study will need to recruit 144 participants (FT = 96, TAU = 48) to detect a change of 0.5.

These sample sizes should be more than sufficient for mixed model repeated measures (MMRM) across the three time points to have > 80% power and also allow for post hoc *t*-tests both between groups and within groups to have ≥ 80% power.

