An unforeseen challenge, in the context of the current study, is the impact of COVID-19. The study has had to be paused for 4 months (March–July 2020) due to the COVID-19 lockdown restrictions in the RoI. This will have a negative impact on recruitment rates and potentially on retention, as several families have contracted COVID-19 and have had to withdraw from the study. In addition, one third of the families recruited, to date, reported that their mental health had worsened as a result of the pandemic, although by the same token, most families were coping well. Furthermore, practitioners are experiencing challenges in resuming clinical practice in terms of their capacity to deliver FT safely including, for example, a lack of suitable rooms in site centres and difficulties in achieving 2-m physical distancing in the family home. Moreover, most MDTs have suffered staff shortages as a result of the ongoing lack of formal and informal childcare supports in the RoI due to COVID-19. The research team are working closely with practitioners and managers to help support them in resuming delivery of FT. Data collection from July 2020 will be undertaken in line with COVID-19 guidelines [68, 69].

In conclusion, the current study will provide an important contribution to the international evidence base in terms of conducting a rigorous effectiveness trial of FT and in producing high-quality data on costs and key implementation factors. Rigorous trials are essential in providing a sound evidence base to inform policy and practice across the world. Given the prevalence and burden of parental mental illness (including the high risk of intergenerational transmission), it is imperative that we identify effective and cost-effective interventions that are capable of being implemented within routine service settings. The current study will also offer a unique perspective on whether it is possible to produce a paradigm change within mental health services and achieve positive outcomes for families within a time-limited national research programme to develop and promote family-focused practice for families where a parent has mental illness.

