## Trial status

The recruitment phase of the study started in March 2019. Recruitment finished on 30th November 2020. It is anticipated that the study will be completed by the end of 2021. This is protocol version 4, 06.08.2020, recruitment timeline was amended twice to take account of Covid-19 restrictions.

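### The 144 families and the 80% power for SCORE-15 are stated as current, although the protocol expects recruitment to suffer and 144 leaves no reserve

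*Protocol article*

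**What the plan says.** The Sample size section derives the trial's size from SCORE-15: "the study will need to recruit 144 participants (FT = 96, TAU = 48) to detect a change of 0.5". The stated inputs are "Assuming *α* = .05" and "80% power, two tailed testing, 15% attrition, and 2:1 allocation". It then concludes: "These sample sizes should be more than sufficient for mixed model repeated measures (MMRM) across the three time points to have > 80% power", and claims at least 80% for post hoc t-tests between and within groups. The Abstract carries the same number forward without qualification: 144 families "will be randomised to either the 7-session Family Talk programme" or standard care.

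Other sections describe the enrolment. Recruitment opened in March 2019, and under Trial status: "Recruitment finished on 30th November 2020". The Recruitment section says "we cannot further extend the enrolment period in order to account for the 4-month suspension caused by the COVID-19 lockdown restrictions", gives the funding timeline as the reason, and expects an effect on recruitment. The Limitations section says of the pause: "This will have a negative impact on recruitment rates and potentially on retention, as several families have contracted COVID-19 and have had to withdraw". Trial status adds that the recruitment timeline was amended twice because of Covid-19. No section gives the number enrolled, an accrual rate, the original closing date, a revised power or a revised detectable effect.

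**The concern.** The sample-size text and the recruitment text were not brought together. One gives 144 and at least 80% power as properties of the trial. The other reports that enrolment has closed and that the pandemic pause was expected to harm it. A reader of the Sample size section alone does not learn that the number behind the power claim is in doubt.

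This matters most for family functioning. It is one of the two primary outcomes, it alone fixes the sample size, and the Background presents it as a main contribution of the trial. If the SCORE-15 result is null, a reader who trusts the stated power will take it as a well-powered negative for an effect of 0.5. Whether that is fair depends on how many families were randomised and analysed, and the document does not say.

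**Working it through.** **Inputs.** From Sample size: d = 0.5, two-sided alpha 0.05, 2:1 allocation, 15% attrition, 144 = 96 + 48. From Recruitment: March 2019 to 30 November 2020, about 21 months. From Participant timeline: a 4-month pause.

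**Formula.** For a two-sample t-test, the noncentrality is d × √(n1·n2/(n1 + n2)), with n1 + n2 − 2 degrees of freedom. Power is the probability that a noncentral t exceeds the two-sided 5% critical value in absolute size.

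**The plan's figure.** With 96 + 48, the noncentrality is 0.5 × √(96 × 48/144) = 2.83, the critical value is 1.977, and power is 80.2%. So 144 reproduces as the number that must be analysed.

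**Reserve.** With 95 + 48, power is 80.1%. With 94 + 47 it is 79.4%. Three families fewer is enough to fall below 80%.

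**The plan's own attrition at full recruitment.** 144 × 0.85 = 122.4, taken as 82 + 41. The noncentrality is 2.61, power is 73.7%, and the effect detectable at 80% power is 0.54. Allowing for 15% loss would have needed 144/0.85 = 170 families.

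**Shortfall scenarios.** The protocol gives no accrual figures, so these rest on an assumption: 144 was planned over 21 months at a uniform rate, and m months of accrual were lost net of any extension. Then N = 144 × (21 − m)/21.

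| Net months lost (assumed) | Families | Power, no attrition | Power, 15% attrition |
|---|---|---|---|
| 0 | 144 | 80.2% (96 + 48) | 73.7% (82 + 41) |
| 1 | about 137 | 78.4% (91 + 46) | 71.3% (77 + 39) |
| 2 | about 130 | 75.9% (87 + 43) | 69.2% (74 + 37) |
| 3 | about 123 | 73.7% (82 + 41) | 66.7% (70 + 35) |
| 4 | about 117 | 71.5% (78 + 39) | 64.1% (66 + 33) |

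At 4 months, the effect detectable at 80% power is 0.55 without attrition and 0.60 with it. The recruitment part alone, read down the no-attrition column, costs 0 to 8.7 points (80.2 − 71.5).

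**The other primary outcome.** At d = 0.7, the lower of the two SDQ effects quoted, 66 + 33 still gives 90% power and 82 + 41 gives 95%.

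**The case against.** The strongest reply is that a target and a disclosed risk to it can both stand. The Sample size section says what the study needs, and no section says that 144 was missed. The two timeline amendments and the word "further" in the Recruitment section's sentence on extension suggest that the window had already been lengthened, so the 21 months may include compensation. Enrolment was staggered and depended on referrals, so uniform accrual is only a device. All of this stands. A reader might infer that 4 of 21 months of accrual were lost, or that the trial closed near 117 families. The documents support neither, and the scenarios have to start at zero.

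A second reply is that the primary analysis is a mixed model that includes baseline, and that the protocol chose the t-test as the least powerful test in its main analysis. This also stands. As an illustration, assume simple covariance adjustment with a baseline-outcome correlation of 0.5: 78 + 39 gives 83% and 66 + 33 gives about 77% at d = 0.5. At a correlation of 0.3, 78 + 39 gives 76%. It would therefore be wrong to conclude that the mixed-model claim is false. It is unsupported, because no correlation or calculation is given.

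A third reply is that the risk is disclosed in two places and that confidence intervals will be reported under CONSORT. That softens the consequence. But neither disclosure is linked to power, and the statement that the sizes are more than sufficient is left as it was.

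**Conclusion.** The point holds as a missing update to a stated property of the design. It is not an arithmetic slip, and it is not proof of under-recruitment. The between-group t-test power for SCORE-15 reaches 80% only if all 144 families are analysed. It is about 74% under the plan's own 15% attrition with full recruitment, and lower with any shortfall: down to 71.5% without attrition and 64% with it at the far end of the assumed range. The attrition part rests only on the protocol's inputs. The shortfall part rests on assumed uniform accrual over 21 months and an unknown net loss of 0 to 4 months. The point concerns family functioning; SDQ at d = 0.7 is little affected.

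**What to change.** In the Abstract and the Sample size section, label 144 (96 + 48) as the original target and state the number of families randomised when recruitment closed. For the number expected to be analysed at 6 months, restate the between-group t-test power at d = 0.5 and the effect detectable at 80% power, and use these in place of the claim of at least 80% for between-group post hoc t-tests. Keep the statement that the mixed model exceeds 80% power only if a calculation at that number, with a stated baseline-outcome correlation, supports it; otherwise remove it.

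The cost is a short recalculation and a few sentences, and probably a less favourable power figure in print. No extra families, visits or data are needed, and no additional recruitment is proposed.

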### Blinding

Due to the nature of the intervention, neither participants nor practitioners can be blinded to allocation. Outcome assessors will be blinded to treatment allocation, as well as those conducting the statistical analyses. Randomisation will be conducted by an external consultant who is unconnected to the recruitment, data collection, or analysis process. Participants (families), and practitioners will be requested not to disclose their group allocation to the research team. Any evidence of unblinding will be taken into account at the analysis stage.

### Data collection

#### Families

Participants will be invited to complete outcome measures at baseline (T0) and at 6- and 12-month follow-up periods (T1 and T2) (Fig. 2). Each questionnaire will be coded with the participant’s ID number, date of completion, version (baseline, T1, T2), and the researcher’s name. Qualitative data (i.e. interviews) will be collected from families following the 6-month assessment within the RCT. Copies of the impact evaluation and costs measures, and interview schedules for the process evaluation, can be obtained from the PRIMERA programme coordinator (https://cmhcr.eu/primera-programme/).

For all aspects of the evaluation (RCT, costs and process evaluations), data will be collected by a researcher who will meet with the participant in the family home, or, if preferred, in a local family/health care centre. Data will also be collected from parents by video call where it is not safe, due to COVID-19, to meet in person. Parents and children (8–18 years) will provide written informed consent/assent prior to data collection and will be assured of ethical protections (e.g. confidentiality) and risks and benefits from participation. Parents will complete a paper version of outcome measures and the assessment will take 45–75 min (with a break if required). Whilst electronic devices may sometimes improve data accuracy and the timeliness of data collection and management [55], the experience of the research team and site staff is that vulnerable populations may be alienated by their use and are more comfortable with paper-based data collection methods. Based on feedback from the mental health service professionals with whom we are working, children will be offered an option of completing a paper version of the survey in the presence of the researcher or via the secure online Qualtrics software package [56]. Both options will take 10–15 min. The online survey will include voice-recorded files in order to assist comprehension. The online survey will be accessed via the project webpage in compliance with *General Data Protection Regulation*s (GDPR). No personal identifiers of children will be collected using Qualtrics and Qualtrics does not share data with third parties [56].

For the qualitative interviews, parents and children will provide consent/assent for their interview to be digitally recorded. Anonymity and other ethical protections will be assured (Information sheets and consent/assent forms are available upon request).

In order to enhance the quality of the data, all fieldworkers will receive standardised training in how to administer the measures with families. In addition, selected fieldworkers will be experienced in collecting data from vulnerable populations. Missing, incomplete, or inaccurate data will be assessed within a week of data collection by the data-input manager, who will liaise with the relevant fieldworkers for information. Families will be re-contacted if necessary for any missing data.

Participant retention will be promoted using the following strategies: scheduling appointments by telephone and reminding participants by text; minimising participant burden during visits; financial reimbursement at each data collection point; and liaising with study sites to locate hard-to-reach parents. Every effort will be made by both the research team and study sites to engage families for the entire study period. Where a participant withdraws consent for one follow-up assessment, they will be asked if they would consent to participate at another time point, or for another element of the study (e.g. the process or costs evaluation). All participants will be included in an intention-to-treat analysis, regardless of adherence or non-retention. Reasons for missing data—both non-adherence (e.g. family crisis, perceived harm or non-efficacy) and non-retention (e.g. consent withdrawn; lost to follow-up)—will be sought from parents and practitioners and will be recorded and interpreted during analysis.

#### Data collection—service providers

Semi-structured interviews (30–60 min), focus groups (60–90 min), and video/phone calls (15–30 min) will be audio recorded with participants’ consent and transcribed verbatim and in full. A secure online Qualtrics survey (lasting 15 min) will be administered on a once-off basis only, to clinicians following FT delivery in order to assess implementation fidelity, participant attendance, and engagement.

#### Data management

Quantitative data will be entered into a database (IBM SPSS Statistics version 26) by a data manager who will conduct regular verification checks and quality audits to ensure accuracy of entry and coding. This process will be overseen by the Programme Coordinator. The data manager will also liaise with fieldworkers to clarify the accuracy of entered data. Qualitative data (i.e. interview and focus-group data) will be transcribed verbatim and stored on a secure, central network, which is encrypted and password-protected. Data will be coded and analysed using the qualitative analysis software package MAXQDA [57].

The study will adhere closely to the GDPR and data protection guidelines on research in the health sector by the Data Commissioner of Ireland [58]. All research staff have received GDPR training. All forms will be anonymised through the allocation of a unique identification number and will be stored under lock and key throughout, and following completion of, the study. All computers will be password-protected and the transfer of any information from laptops to the secure central network will be carried out with extreme caution. Encryption software will also be used to encrypt sensitive data which are stored electronically. Encrypted data will be accessible using a key which will only be known to the research team members. A separate (password-protected) database of names and contact details will be stored away from the other data and there will be no means of linking the two.

Where participants provide consent/assent, an anonymised version of their data will be placed in the Irish Qualitative Data Archive (IQDA) and the Irish Social Sciences Data Archive (ISSDA) so that it may be used by future researchers if so required. Future researchers will require ethical approval for their study to proceed. In all other instances, data will be destroyed 10 years after the completion of the study; manual data will be shredded confidentially and electronic data will be reformatted or overwritten.

#### Statistical methods

Data presentation and results will be carried out according to Consolidated Standards of Reporting Trials (CONSORT) guidelines for RCTs. Descriptive statistics (means, standard deviations, frequencies) will be used to describe the pre-treatment characteristics of participants and for primary and secondary outcome measures at each time point. Mixed model repeated measures (MMRM) will be used to investigate the effects of the intervention at two between (intervention and control) and three within (pre-intervention, 6- and 12-month follow-ups) levels for all primary and secondary outcome measures (all continuous outcome data). Initial MMRM analysis will control for baseline psychopathology as a fixed covariate. Modelling for the primary outcomes will be conducted using an unstructured repeated measures covariance matrix and all other variables as fixed effects. Mean difference effect sizes, 95% CIs, and *p* values will be reported for continuous outcomes. Where parametric test assumptions fail significantly, then non-parametric tests will be used.

MMRM was chosen as the primary method for analysis as it can reduce several analytic problems that may arise within the current study. Firstly, it allows for different numbers of measurements per participant, thereby tolerating a level of missing data, which is particularly problematic with RCTs with vulnerable populations, as follow-up data are often collected many months after treatment has ended and participants may be difficult to contact [59]. This enables us to use all of the data collected as opposed to deleting cases or imputing missing values. Secondly, it has the advantage of modelling change within individuals as well as across groups. Singer and Willet [60] identify this as the best approach for longitudinal data that has three or more time points.

The analysis will follow an intention-to-treat (ITT) principle where all randomised participants, including those who stop receiving the intervention, will be analysed ‘as randomised’. MMRM analysis is a maximum likelihood statistical modelling technique whereby mean estimates and the repeated measures covariance structure for the observed data are based on a statistical model and possible values are generated for the missing data [61]. Attrition will also be analysed to assess the differences between those who ‘dropped out’ and those who stayed, and to assess if there are predictors at baseline to indicate differences. Qualitative data will also inform the identification of predictor variables for attrition. MMRM will be the primary analytic method, although *t*-tests will be used to provide detail on any significant differences found from the MMRM.

Regression techniques will be used to explore whether intervention effects differ for certain participant groups such as age of children, severity of parental mental illness, other parent also has a mental illness, and socioeconomic status. Analysis will be conducted using SPSS software (IBM SPSS Statistics version 26).

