### Outcomes

This study involves an RCT, and associated costs and process evaluations. The primary and secondary outcomes for the impact evaluation are outlined below, followed by the data collection measures for the costs and process evaluations. All measures for the impact evaluation are based on a continuous scale and will be analysed using covariance adjusted outcomes. All outcome measures for the impact evaluation will be collected at baseline and at 6- and 12-month follow-ups. All children who complete the child-report measures will be over 8 years old. Figure 2 provides an overview of primary and secondary outcomes and data collection points.

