### Participant timeline

The flow of participants from recruitment through to the end of the study is shown in Fig. 2. Parents and children will be assessed at T0 (pre-intervention), at 6-month follow-up (T1; 3 months post intervention), and at 12-month follow-up (T2). Assessment of the control group will continue up to T1, after which they will be offered FT. Assessment of the intervention group alone will continue at 12-month follow-up. Enrolment into the study will be on a staggered basis and will depend on clinicians referring suitable families to the research team.

Data collection and delivery of the intervention were necessarily paused for 4 months (mid-March to mid-July 2020) due to the COVID-19 lockdown restrictions in the RoI. Therefore, assessments affected by the restrictions will be collected 4 months later than originally planned. However, taking the pause into account, we still consider the assessment time points to be 6- and 12-month follow-up. Assessments affected by the COVID-19 suspension will be noted in the analysis.

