### Limitations

Based on experiences in other countries in implementing FFP, we expect some difficulties in recruiting families to the trial [67]. FFP for this population has traditionally not been practised within mental health settings within the RoI [9]. Whilst participating sites have been given a considerable amount of time to instal and implement FT prior to recruiting participants for the RCT, systemic barriers still exist, including, for example, practitioner workload and turnover, and a persistent perception amongst some AMHS and CAMHS personnel that FFP is a ‘luxury’ preventive issue and that family support is not their priority or their remit. In addition, we anticipate that some parents with mental illness may not be comfortable in coming forward for help, given the double stigma of having a mental illness and revealing struggles in parenting. As indicated earlier, we have already invested considerable time and effort in raising awareness amongst practitioners and management of the need to support this population and to promote FT in their communities. We have also promoted FFP in local and national media through various fora including print and social media, radio, and television. In order to promote family engagement, clinicians are urged, where possible, to offer families a choice in delivering FT either within the local community clinic or family home setting.

The current study is also limited in that we can only conduct a 6- and 12-month follow-up within the allotted funding timeframe. Evidence from previous evaluations suggests that benefits tend to accumulate and improve in the longer term; for instance, Beardslee and colleagues found that child and parent mental health outcomes improved at 4.5 year follow-up compared with the 1.5 year follow-up [25]. However, previous evaluations have reported benefits at post intervention and at 18-month follow-up [26, 27] so it is hoped that differences (if they exist) can be detected at 6- and 12-month follow-up within the current study, and indeed, these time points are commonly used in the evaluation of psychosocial programmes [21].

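### The main mixed model is set out as two groups by three times, but controls are not assessed at 12 months, so no 12-month between-group effect can be estimated

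*Protocol article*

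**What the plan says.** The Trial design section places the primary endpoint (child psychosocial functioning and family functioning) at 6 months. The Statistical methods section makes a mixed model for repeated measures the primary method and fits it to both arms, intervention and control, at "three within (pre-intervention, 6- and 12-month follow-ups) levels for all primary and secondary outcome measures". For the primary outcomes it adds: "Modelling for the primary outcomes will be conducted using an unstructured repeated measures covariance matrix and all other variables as fixed effects". The Sample size section ends by claiming more than 80% power for this model over all three assessments.

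The Participant timeline gives a different schedule: "Assessment of the control group will continue up to T1, after which they will be offered FT". It continues: "Assessment of the intervention group alone will continue at 12-month follow-up". The objectives section confirms that controls are on a waitlist and are offered the programme after the 6-month assessment.

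Other sections mention 12 months without limiting it to one arm:

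- Outcomes: "All outcome measures for the impact evaluation will be collected at baseline and at 6- and 12-month follow-ups".
- Abstract, Methods: "Blind assessments will take place at pre-intervention and at 6- and 12-month follow-up".
- Data collection (Families) invites participants to complete measures at T0, T1 and T2.
- Limitations expresses the hope that "differences (if they exist) can be detected at 6- and 12-month follow-up within the current study".
- Dissemination plans a paper on 6- and 12-month outcomes.

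No section says that the 12-month analysis is within-group only.

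**The concern.** The model and the schedule cannot both be followed as written. If control families have no T2 data, the model has no information on what their 12-month mean would be, and no randomised comparison exists at that time. An analyst following the Statistical methods section would meet a contrast that cannot be estimated, or would fall back on the only 12-month test available, which is pre-post change in the Family Talk arm. That change would include natural recovery, regression to the mean and pandemic effects as well as any effect of the programme. The protocol reports a four-month pause, and worse mental health in one third of the families recruited so far, so the bias could go in either direction.

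Two further statements depend on the same gap. The three-assessment power claim cannot refer to a 12-month group effect. The promise of blinded 12-month assessment also fails, because a family seen at T2 is by that fact a Family Talk family.

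**Working it through.** **1. The plan's own figure.** The 144 families (96 + 48) come from a two-sample t-test at one time point with d = 0.5, two-sided alpha 0.05 and 2:1 allocation. The noncentrality is 0.5 / sqrt(1/96 + 1/48) = 0.5 × sqrt(32) = 2.83, and the exact noncentral t distribution gives 80.2% power. This reproduces 144 only if every family is analysed. With the stated 15% attrition, 96 × 0.85 = 81.6 and 48 × 0.85 = 40.8, or about 82 + 41. The noncentrality is then 2.61 and power is 73.7%. The calculation is a single comparison of two arms. The Sample size section shows none for three time points.

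**2. Cells observed under the Participant timeline.**

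| Arm | T0 | T1 (6 months) | T2 (12 months) |
|---|---|---|---|
| Family Talk | yes | yes | yes |
| Control | yes | yes | none |

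**3. Estimability.** Write the mean as b0 + b1·G + b2·T1 + b3·T2 + b4·G·T1 + b5·G·T2. This has 6 parameters. The five observed cells give a design matrix of rank 5. A contrast can be estimated only if it lies in the row space of that matrix.

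| Contrast | Coefficients | Estimable? |
|---|---|---|
| Group difference at 6 months | b1 + b4 | yes |
| Group × T1 | b4 | yes |
| Within-Family Talk change, T0 to T2 | b3 + b5 | yes |
| Group difference at 12 months | b1 + b5 | no |
| Group × T2 | b5 | no |
| Group effect averaged over three times | b1 + (b4 + b5)/3 | no |

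With baseline as a covariate and only T1 and T2 as responses, the rank is 3 of 4. Again the T1 difference can be estimated and the T2 difference cannot. An additive model without interaction has full rank (4 of 4), but it supplies a 12-month group effect only by assuming that the effect is the same at every time.

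**4. Do the T2 data disturb the 6-month contrast?** Every T2 record belongs to the Family Talk arm. Adding a constant c to all T2 responses adds c times the T2 indicator column. In a generalised least squares fit with a given covariance, this moves only the coefficient that carries T2 and leaves b1 and b4 as they were. A numerical check with 82 + 41 families and shifts of 0, 0.3 and 1 SD agreed to eight decimals. The interaction that remains has 5 − (1 + 1 + 2) = 1 degree of freedom, which is the randomised T0-to-T1 contrast.

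**5. How often would a one-arm 12-month change look significant with no treatment effect?** The documents do not give natural improvement m (in SD units) or the T0–T2 correlation r, so both are assumed over a range. With n = 82, the SD of change is sqrt(2(1 − r)), the noncentrality is m × sqrt(82) / sqrt(2(1 − r)), and the test is a two-sided paired t-test on 81 degrees of freedom.

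| m | r = 0.5 | r = 0.7 |
|---|---|---|
| 0 | 5% | 5% |
| 0.1 | 15% (noncentrality 0.91) | 21% (1.17) |
| 0.2 | 43% (1.81) | 64% (2.34) |
| 0.3 | 77% (2.72) | 93% (3.51) |

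**The case against.** The strongest defence is that the primary result is safe. The endpoint is fixed at 6 months, that contrast can be estimated from the model as written, and the cost-effectiveness comparison is confined to 6 months. All of this stands. The waitlist is openly described, the Sample size section foresees within-group tests, and the analysis rationale mentions change within individuals. Within-arm use of T2 is therefore anticipated, although it is never stated to be the only use.

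A reader might infer that 12-month change in the Family Talk arm leaks into the group effect or the interaction. Step 4 shows that it does not; only the T2 time coefficient carries it. A reader might also infer that the model fails to address the 6-month endpoint. It can address it. The Statistical methods section simply does not single that contrast out as the primary test. Nor does the protocol say that a one-arm change will be read as efficacy. The Limitations sentence is a hope and does not specify a between-group difference. The percentages in step 5 therefore describe a possible misreading, not a prescribed analysis.

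Two defences do not stand. The likelihood handling of missing data copes with incomplete families, but it cannot supply a mean that is unobserved in a whole arm by design. And if the Outcomes section were read as adding control assessments at 12 months, those families would already have been offered Family Talk, so the contrast would be early against delayed programme and not programme against usual care.

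**Conclusion.** The point holds as a contradiction between the analysis model and the assessment schedule. Three quantities that a two-by-three model invites cannot be estimated: the 12-month group difference, the group-by-12-month term and the group effect averaged over three times. This is structural (rank 5 of 6) and does not depend on sample size. It assumes only that the Participant timeline is the schedule actually followed.

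The 6-month randomised comparison is neither lost nor biased. What is at risk is the meaning of anything reported at 12 months. Such a result is uncontrolled, and under the assumed range (82 families, improvement of 0.1 to 0.3 SD, correlation 0.5 to 0.7) it would reach significance without any treatment effect in about 15% to 93% of trials. The three-assessment power claim is unsupported for a 12-month group effect, and the claim of blinded assessment does not hold at T2.

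**What to change.** 1. In Statistical methods, name the between-group contrast at T1 (6 months) as the primary test. The Family Talk T2 data may stay in the model or be left out; keeping them does not bias the T1 contrast and, if data are missing at random, may help with families who missed T1.
2. Report T2 only as within-arm maintenance in the Family Talk group, with no between-group p-value and no efficacy claim.
3. In Sample size, restate the mixed-model power claim for the 6-month contrast only. On the plan's own t-test basis, power at d = 0.5 is 80.2% with all 144 families and 73.7% with about 82 + 41.
4. Bring the Abstract, Outcomes, Data collection (Families), Statistical methods and Limitations into line with the Participant timeline by stating that T2 covers the intervention arm alone.
5. Remove the claim of blinding for T2.

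The cost is wording only: no new data and no change to the primary comparison. The trial gives up a 12-month efficacy claim that its design cannot support.
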